## Data collection and quality control

The Sponsor is responsible for implementing and maintaining a quality management system with written development procedures and functional area standard operating procedures (SOP) to ensure that studies are conducted and data are generated, documented, and reported in compliance with the protocol, accepted standards of Good Epidemiological Practice (GEP) [16], and all applicable laws, rules and regulations relating to the conduct of the registry.

Before the registry starts at the sites, all investigators will be sufficiently trained on the background and objectives of the study and ethical as well as regulatory obligations.

Data will be collected by the centers online, using a secure connection. No paper pencil CRFs will be used. The electronic data capture system (EDC) with electronic data collection forms (eCRFs) and other features (e.g., repository of registry documents) will be provided by the sponsor. No software applications need to be installed by the sites. The web-based EDC application is password protected. User account requests are authorized by GWT. A manual with instructions how to use the EDC will be made available to sites.

The data will be entered by the investigator or registry site personnel via a secure internet connection into the registry database. Only these persons can record or change data relating to patients in their center on the CRFs.

Detailed information on checks for completeness, accuracy, plausibility and validity are given in the Data Management Plan (DMP). The same plan will specify measures for handling of missing data and permissible clarifications. The DMP is available upon request.

Upon entry, the data is automatically checked for completeness and plausibility.

As part of the statistical processing, the data is checked again and queries are sent to the Centre if necessary. If needed, requests will be sent to the sites to correct incorrect inaccurate data or complete missing data.

In about 10% of the centers, an audit will be carried out to check the correct data entry while respecting data protection (monitoring with comparison of the registry data with original patient data).

## Statistical considerations

### Sample size

As the present registry has mainly descriptive aims, there is no formal power calculation needed to determine the target sample size [17]. Rather, the sample size is determined by feasibility aspects.

From a drug safety angle, an enrolled number of 900 patients according to the “rule of three” will allow for the detection of ADR occurring at an incidence of 1 in 300 person-years [18, 19]. If the median observation duration is 2.5 years, an ADR occurring with an incidence of 1 in 750 person-years will be detected.

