**Methods/Design:**

INSIGHTS-ILD is a prospective observational longitudinal registry designed to describe characteristics, management and course of newly diagnosed (incident) and prevalent patients with fILD on the long term. The registry uses a non-probability sampling approach to collect data on characteristics, therapeutic interventions, health-related quality of life and health economic parameters. It is planned to include 900 patients in ambulatory care in about 30 expert sites over three years. The study has been initiated in December 2021, and currently (January 2023) follows 360 patients.

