Comparison of patients treated with and without antifibrotic therapy in terms of mortality, pulmonary function test results and other outcomes will be performed on group level and not on single drug level (nintedanib, pirfenidone) as described in the following. The entire observation period will be considered for each patient in the registry in order to compare outcomes of interest. The observation time will start for each patient at registry enrolment in order to avoid immortal time bias (= “waiting time bias” bias due to exposure misclassification). Patients may start and stop new treatments such as antifibrotic therapy during follow-up. All available treatment episodes reported in the registry will be used in order to analyze the association between treatments and outcomes. At least two treatment periods will be assigned to patients who started antifibrotic therapy during follow-up; namely, a treatment period without antifibrotic therapy after enrolment, and another with antifibrotic therapy after treatment initiation. The episode before the start of antifibrotic therapy will be included in the mortality and other outcome analyses of the “no antifibrotics” group to account for immortal time bias. The analyses will be performed by generalized mixed models including time-dependent covariates. All analyses are planned on the group level (antifibrotic therapy yes / no), the exposition time to any antifibrotic therapy is used for analyses. Information on the specific drug is descriptively provided (percentage of patients on the drugs at BL, 6, 12, 18, 24 and 30 months). Detailed information (on product, dose and treatment dates) on previous (and current) therapy for pulmonary fibrosis will be collected.

Comparison of the two treatment groups in terms of lung function data and 6MWD test results will be analyzed by propensity score weighted linear mixed models to account for the possibility of more than one treatment episode for a single patient (additional cluster variable), and to account for the longitudinal study design, which was based on observed values. Intention to treat analyses will be additionally performed if it will be appropriate.

Further statistical methods planned include propensity score technique, multiple imputations, competing risks analyses, and latent class analysis to determine cluster of patients.

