## Discussion

The study has been registered in the NIS registry of the BfArM under NIS7562, and in the DRKS registry under DRKS00027389. Study results will be reported after termination of the project on the BfArM website as Clinical Study Report. The results of this registry are intended to be published in a series of articles in peer-reviewed journals and as abstracts/presentations at medical congresses under the oversight of the sponsor. Current guidelines and recommendation on good publication practice will be followed (e.g. STROBE [21]).

The study was initiated by investigators (see authors), the legal sponsor is the GWT-TUD in Dresden. The study entered the field phase in December 2021, and has included 360 patients to date (11 January 2023). The field (documentation) phase of the study is planned until December 2024. All study materials are available in English.

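### The 1-in-750 person-years ADR limit assumes a 2.5-year median observation that the registry's own accrual and end date rule out; the ceiling is 1 in 725, and plausible accrual gives about 1 in 460 to 1 in 570

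*Protocol article*

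**What the plan says.** The Sample size section bases the number of patients on feasibility and then adds a drug-safety remark. It says that "an enrolled number of 900 patients according to the “rule of three” will allow for the detection of ADR occurring at an incidence of 1" (the denominator that follows is 300 person-years). Its next sentence reads: "If the median observation duration is 2.5 years, an ADR occurring with an incidence of 1 in 750 person-years will be detected".

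Four other statements in the article determine how much observation time can accrue:

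- Abstract, Methods/Design: "It is planned to include 900 patients in ambulatory care in about 30 expert sites over three years".
- Discussion, on accrual: "The study entered the field phase in December 2021, and has included 360 patients to date (11 January 2023".
- Discussion, on the end: "The field (documentation) phase of the study is planned until December 2024".
- Descriptive analysis and statistical testing: "The observation time will start for each patient at registry enrolment".

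Under Visit schedule and assessments, follow-up of a patient ends at termination of the registry or at death. Under Safety reporting, and in the safety row of Table 2, the ADR reporting duty applies to patients receiving nintedanib.

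**The concern.** A median of 2.5 years in a registry whose documentation lasts about three years requires half the patients to enter in roughly the first seven months. The article's own count shows that this did not happen. The 1-in-750 limit therefore rests on a condition that had already failed when the article was written.

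Assessing safety is a listed objective in Table 1, and this remark is the only quantitative statement of what 900 patients can deliver for it. If a rare ADR is not seen, readers may cite 1 in 750 as the level of reassurance, and the data will support less than that.

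**Working it through.** **Inputs.** N = 900 and a 2.5-year median (Sample size); start in December 2021, 360 patients by 11 January 2023, documentation until December 2024 (Discussion); observation counted from enrolment (Descriptive analysis and statistical testing). Where only a month is given, the most generous day is used: start 1 December 2021, end 31 December 2024.

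**Step 1: reproduce the plan's figures.** The rule of three sets the detectable rate at 3 / person-years, because exp(−3) ≈ 0.05 leaves about a 95% chance of at least one case.

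- One year per patient: 900 × 1 / 3 = 300.
- 2.5 years per patient: 900 × 2.5 / 3 = 750, from 2,250 person-years. P(at least one case at 1 in 750) = 1 − exp(−2,250/750) = 95.0%.

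Both figures reproduce. The arithmetic is right; the follow-up input is the problem.

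**Step 2: can the median be 2.5 years?**

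- Longest possible observation, 1 December 2021 to 31 December 2024: 1,126 days / 365.25 = 3.083 years.
- Longest possible for anyone entering after 11 January 2023: less than 720 days / 365.25 = 1.971 years.
- A 2.5-year median needs about 450 patients enrolled by 2 July 2022. Six months after that date there were 360.
- The 450th patient therefore enters after 11 January 2023, and the median is below 1.97 years before any death or loss.

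**Step 3: ceiling on total observation.** Suppose all 360 entered on the first day, the other 540 all entered on 11 January 2023, and nobody left:

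360 × 3.083 + 540 × 1.971 = 1,110 + 1,064 = 2,174 person-years; 2,174 / 3 = 725.

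P(at least one case at 1 in 750) = 1 − exp(−2,174/750) = 94.5%. If documentation ended on 1 December 2024 instead, the ceiling would be 2,100 person-years, or 1 in 700.

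**Step 4: scenarios.** Accrual after January 2023 is not in the article, so these patterns are assumptions. None includes attrition.

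| Assumed accrual of 900 patients | Median (years) | Person-years | Limit | P(≥1 case at 1 in 750) |
|---|---|---|---|---|
| Even over the whole period (planned pace, ignoring the reported 360) | 1.54 | 1,387 | 1 in 462 | 84% |
| 360 evenly to 11 January 2023, 540 evenly to December 2024 | 1.64 | 1,442 | 1 in 481 | 85% |
| Observed pace, about 27 per month, until 900 | 1.69 | 1,524 | 1 in 508 | 87% |
| 360 evenly, 540 evenly by December 2023 | 1.81 | 1,712 | 1 in 571 | 90% |

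For the observed pace: 360 in 406 days (1.112 years) is 324 per year, so 900 are reached after 2.78 years. Mean observation is 3.083 − 2.78/2 = 1.69 years, and 900 × 1.69 gives about 1,524 person-years.

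**Step 5: end date that a 2.5-year median would need.** If the 450th patient entered on 12 January 2023, documentation would have to run to mid-July 2025. At the observed pace, the 450th enters in late April 2023 and documentation would have to run to about October 2025.

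**Step 6: whose time counts.** All the totals above are observation time for all 900 patients. ADR reporting is required only while patients receive nintedanib, and their share is not given. Drug-exposed time cannot exceed these totals and is lower if any patient is off the drug. No figure can be put on the difference.

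**The case against.** The strongest reply has four parts.

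- **The sentence is conditional and correctly calculated.** True. But the Discussion rules the condition out, so the result does not describe this registry.
- **The sample size does not rest on it.** This stands. The article says that feasibility fixes the number and that no power calculation is needed. The remark sets no endpoint, analysis or decision rule. This limits the severity but does not remove the contradiction.
- **What the documents alone prove is small.** This also stands. The ceiling of 1 in 725 is about 3% short of 750 (725/750 = 0.967), with a 94.5% rather than 95% chance of at least one case. The larger shortfall depends on assumed accrual.
- **December 2024 is only a plan, or might close enrolment alone.** The Discussion applies that date to documentation, and the article states no later one. If longer follow-up is intended, saying so would resolve the conflict.

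A reader might also infer further errors from the same text, but these are not errors of substance. The 1-in-300 figure takes one year per patient, an unstated but attainable average. The claim of detection without a probability is loose, but the named rule conventionally implies 95%. The tabulation of drug use up to 30 months ("percentage of patients on the drugs at BL, 6, 12, 18, 24 and 30 months") does not claim that all 900 patients reach that point. Person-years do depend on the mean rather than the median, but in the observed-pace scenario both are 1.69 years.

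**Conclusion.** The point holds, with moderate severity. For 900 patients and documentation ending in December 2024, the 2.5-year median cannot occur and the 1-in-750 limit cannot be reached. The median is below 1.97 years, and the limit is at best 1 in 725. That bound needs no assumption beyond the article's dates and counts, read generously.

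The size of the practical shortfall is less certain. About 1 in 460 to 1 in 570, with an 84–90% chance of at least one case at a true rate of 1 in 750, rests on assumed accrual after January 2023 and on no attrition. Deaths, losses and the restriction of ADR reporting to nintedanib all make it less favourable.

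A reader might infer a single replacement value near 1 in 500 per person-year of drug exposure, or that 900 patients are too few. The documents support neither. Later accrual and the nintedanib share are not given, and the number of patients is set by feasibility. The conclusion would change only if documentation ran beyond December 2024 or clearly more than 900 patients were enrolled; the article states neither.

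**What to change.** Choose one of two routes in the Sample size section.

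1. **Reconcile the inputs.** If longer follow-up is intended, state the end of follow-up separately from the end of enrolment and show that it yields the 2,250 person-years behind 1 in 750. A 2.5-year median alone would need documentation until mid-July 2025 at the earliest. This route costs additional registry time.
2. **Restate the limit.** Derive it from total person-years (mean observation × number of patients). Give a scenario range, such as about 1 in 460 to 1 in 570 before attrition, with the accrual and attrition assumptions labelled and the ceiling of 1 in 725 stated. Express it as an approximately 95% probability of observing at least one case. This costs only wording and a less favourable figure.

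Under either route, add that ADR reporting is required only for patients receiving nintedanib, so the limit for drug-exposed time is less favourable than the one for all registry observation time. Give that limit once the share of exposed time is known. The target of 900 patients need not change.

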### Descriptive analysis and statistical testing

Data will be analyzed in 6-month intervals in order to keep sites appraised of the progress of the registry and to review data quality (rate of missing values, data distribution, outliers).

Concomitant medication will be coded using the WHO Drug Dictionary and tabulated by ATC term. Medical history, concomitant diseases and ADR will be coded by MedDRA in its current version [20].

All background variables and outcome parameters will be analyzed descriptively at baseline and each subsequent follow-up assessment with appropriate statistical methods: categorical variables by frequency tables (absolute and relative frequencies) and continuous variables by summary statistics (i.e., mean, standard deviation, minimum, median, quartiles and maximum). Continuous variables will also be described by absolute value and as change from baseline per analysis time point, if applicable. The primary endpoint as well as secondary endpoints will be analyzed in regular intervals.

Analyses will be performed for the total study population (overall analysis) and separately by indication or relevant subgroups (e.g., PPF groups, age, sex, pretreated and newly treated patients), if patient numbers are sufficient. Pretreated patients are here defined as patients already on treatment when enrolled in the study, whereas newly treated patients will be patients newly starting ILD treatment.

Survival outcome and clinical events such as exacerbations will be analyzed by Kaplan Meier estimates. Association of mortality and clinical events with parameters of interest will be analyzed by Cox proportional hazard model with time-invariant and time-dependent covariates. The change in lung function parameters (FVC, DLCO), 6MWD, QoL and days of hospitalization will be modeled by generalized linear mixed models to account for the longitudinal data. Potential predictor variables will be included into the generalized linear mixed models to determine correlates for the analyzed outcome variables. The change in treatment strategy and drug utilization (dose and dosing schedule, duration of treatment (persistence), switches between treatments, phases without drug treatment, and reasons for drug discontinuation) will be descriptively reported. Exploratory analyses will be performed in order to determine associations of biomarkers with the defined outcome variables.

Comparison of patients treated with and without antifibrotic therapy in terms of mortality, pulmonary function test results and other outcomes will be performed on group level and not on single drug level (nintedanib, pirfenidone) as described in the following. The entire observation period will be considered for each patient in the registry in order to compare outcomes of interest. The observation time will start for each patient at registry enrolment in order to avoid immortal time bias (= “waiting time bias” bias due to exposure misclassification). Patients may start and stop new treatments such as antifibrotic therapy during follow-up. All available treatment episodes reported in the registry will be used in order to analyze the association between treatments and outcomes. At least two treatment periods will be assigned to patients who started antifibrotic therapy during follow-up; namely, a treatment period without antifibrotic therapy after enrolment, and another with antifibrotic therapy after treatment initiation. The episode before the start of antifibrotic therapy will be included in the mortality and other outcome analyses of the “no antifibrotics” group to account for immortal time bias. The analyses will be performed by generalized mixed models including time-dependent covariates. All analyses are planned on the group level (antifibrotic therapy yes / no), the exposition time to any antifibrotic therapy is used for analyses. Information on the specific drug is descriptively provided (percentage of patients on the drugs at BL, 6, 12, 18, 24 and 30 months). Detailed information (on product, dose and treatment dates) on previous (and current) therapy for pulmonary fibrosis will be collected.

Comparison of the two treatment groups in terms of lung function data and 6MWD test results will be analyzed by propensity score weighted linear mixed models to account for the possibility of more than one treatment episode for a single patient (additional cluster variable), and to account for the longitudinal study design, which was based on observed values. Intention to treat analyses will be additionally performed if it will be appropriate.

Further statistical methods planned include propensity score technique, multiple imputations, competing risks analyses, and latent class analysis to determine cluster of patients.

All statistical details including calculated variables and proposed format and content of tables will be detailed in the SAP, which will be finalized before study database lock.

## Discussion

The study has been registered in the NIS registry of the BfArM under NIS7562, and in the DRKS registry under DRKS00027389. Study results will be reported after termination of the project on the BfArM website as Clinical Study Report. The results of this registry are intended to be published in a series of articles in peer-reviewed journals and as abstracts/presentations at medical congresses under the oversight of the sponsor. Current guidelines and recommendation on good publication practice will be followed (e.g. STROBE [21]).

The study was initiated by investigators (see authors), the legal sponsor is the GWT-TUD in Dresden. The study entered the field phase in December 2021, and has included 360 patients to date (11 January 2023). The field (documentation) phase of the study is planned until December 2024. All study materials are available in English.

## Data Availability

Data sharing is not applicable to this article as datasets are being generated but have not been analyzed during the current study.

## Abbreviations

6-MWD: 6-Minute Walk Distance
AE: Adverse Event
ADR: Adverse Drug Reaction
BAL: Bronchoalveolar lavage
BfArM: Bundesinstitut für Arzneimittel und Medizinprodukte (BfA
BMI: Body Mass Index
CI: Confidence Interval
cHP: Chronic hypersensitivity pneumonitis
CRP: C-reactive protein
DL_CO_: Diffusion capacity for carbon monoxide
DRKS: Deutsches Register Klinischer Studien
eCRF: Electronic Case Report Form
EDC: Electronic Data Capture
ESC: European Society for Cardiology
ERS: European Respiratory Society
FVC: Forced vital capacity
GDPR: General Data Protection Regulation
GEP: Good Epidemiological Practice
GWT: Gesellschaft für Wissensschafts- und Technologietransfer
HRCT: High resolution chest computer tomography
ICF: Informed Consent Form
ICMJE: International Committee of Medical Journal Editors
IEC: Institutional Ethics Committee
EOO: End of observation
IIP: Idiopathic interstitial pneumonia
ILD: Interstitial lung disease
INN: International Nonproprietary Name
IPF: Idiopathic pulmonary fibrosis
LTOT: Long-term oxygen therapy
LTx: Lung transplantation
MMF: Mycophenolate mofetil
NHLBI: National Heart, Lung, and Blood Institute
NIS: Non-interventional Study
NYHA: New York Heart Association
PRO: Patient related outcomes
SAE: Serious Adverse Event
SAP: Statistical Analysis Plan
SIC: Subject Identification Code
SmPC: Summary of Product Characteristics
SOP: Standard Operating Procedures
STROBE: Strengthening the Reporting of Observational Studies in Epidemiology
TLC: Total lung capacity
Pa_O2_: Oxygen pressure
PF-ILD: Progressive fibrosing interstitial lung disease
PPF: Progressive pulmonary fibrosis
QoL: Quality of life
UIP: Usual interstitial pneumonia
VO_2max_: Maximal oxygen consumption
WHO: World Health Organization
